## Abstract

**Background:**

Cost control and usage regulation of medical materials (MMs) are the practical issues that the government pays close attention to. Although it is well established that there is great potential to mobilize doctors and patients in participating MMs-related clinical decisions, few interventions adopt effective measures against specific behavioral deficiencies. This study aims at developing and validating an independent consultation and feedback system (ICFS) for optimizing clinical decisions on the use of MMs for inpatients needing joint replacement surgeries.

**Methods:**

Development of the research protocol is based on a problem or deficiency list derived on a trans-theoretical framework which incorporates including mainly soft systems-thinking, information asymmetry, crisis-coping, dual delegation and planned behavior. The intervention consists of two main components targeting at patients and doctors respectively. Each of the intervention ingredients is designed to tackle the doctor and patient-side problems with MMs using in joint replacement surgeries. The intervention arm receives 18 months' ICFS intervention program on the basis of the routine medical services; while the control arm, only the routine medical services. Implementation of the intervention is supported by an online platform established and maintained by the Quality Assurance Center for Medical Care in Anhui Province, a smartphone-based application program (APP) and a web-based clinical support system.

**Discussion:**

The implementation of this study is expected to significantly reduce the deficiencies and moral hazards in decision-making of MMs using through the output of economic, efficient, sustainable and easy-to-promote cooperative intervention programs, thus greatly reducing medical costs and standardizing medical behaviors.

***Trial registration number*:**

ISRCTN10152297.

## Background

With increasing demand for health services and rapid development of new medical technology worldwide, the dependence of clinical medical practice on medical materials (MMs) is growing [1]. High-value MMs account for more than half of total hospital MMs cost [2–4], extensive use of these MMs inevitably incurs great cost burden on hospitals and patients. More importantly, outside the scope of social medical insurance also means lack of third-party medical supervision [5–8]. In recent years, China government has enacted a series of policies focusing on the control of drug use and clinical diagnosis and treatment procedures, which make use of MMs an effective "alternative" for meeting certain policy requirements. For example, caped proportion of medication expense in overall cost is a widely adopted policy. Therefore, increased MMs use means decreased chance of bringing this policy [9, 10]. In order to address high MMs cost, China government has enacted a range measures such as "zero marks for medicines prescribed in hospitals", "centralizing procurement" and "minimum market relays". Some researchers have proposed "GPO (group purchasing organizations) procurement", "procurement alliance" and "zero inventory management". However, these measures have limited effect on curbing the rapid growth of MMs cost. These measures focus primarily on MMs supply with little attention being paid to decision-making process behind MMs use. Clinical decision-making happens in a complex and tricky context featuring medical uncertainty, information asymmetry and fragmented doctor–patient relationship and there are extensive variations and defects in doctors’ and patients’ response to these features [11–13]. Being the "dual delegate" for patients and the third-party payers, doctors are prone to various irrational conducts which are hardly detectable due to great information asymmetry, For example, doctors may order sophisticated examinations mainly for excluding some rare cases and thus reducing medical uncertainty and protecting themselves from credit loss or legal actions. Doctors may be selective in soliciting, recording and giving out information that leads to certain preferred clinical procedures [14–17]. By comparison, patients assume a much disadvantageous position in doctor–patient interactions. Patients are seldom allowed to convey detailed symptoms, history, fears and preferences in limited encounters with their doctors [18]. Patients lack medical knowledge for assessing the benefits and dis-benefits of different diagnosis and treatment procedures [19, 20]. In addition, patients often have various misperceptions of their doctors and vice versa [21, 22].

Contemporary interventions aimed at modifying clinical behavior focus primarily on education, information feedback, and reminders [23]. Many studies demonstrate that carefully designed continuing medical education (CME) courses can effectively improve doctors' use of diagnosis and treatment procedures [24–28]. With the rapid development of communication technology, the proportion of CME that uses the Internet (such as distance education, tele-consultation) is growing among young doctors. Interactive online technologies have proved to be able to change the way of medical education as well as clinical practice [29–32]. Although patients are disadvantageous as compared with doctors in terms of medical knowledge, they directly or indirectly affect clinical decisions in a variety of ways. Given that clinical decision-making is closely linked to patients’ health and expenses, there is great potential to mobilize patients in participating and optimizing clinical decisions [33]. Ringdal et al. reproted that promoting patient participation begins by understanding the patients’ unique preferences and needs for care, establishing a good relationship and paying attention to each patient’s ability to participate despite their illness [34]. D’Agostino and colleagues’ research results suggested that communication training is an effective approach to increase patients’ total level of active participation in healthcare interactions and that some communication behaviors may be more amenable to training (e.g., expressing concerns) [35].

## Study aims

This study aims primarily at developing and validating an independent consultation and feedback system (ICFS) for optimizing clinical decisions on use of MMs for inpatients needing joint replacement surgery. A secondary aim of this study is to conceive and refine a practical framework for identifying and tackling deficiencies in MMs-related decision-making on both doctor and patient side.

## Methods/design

### Study design and sampling

The study validates the effectiveness of the ICFS through a cluster randomized controlled trial (RCT) in Anhui, an inland province located in Eastern China with a population of 63.7 million and 1290 hospitals spread over 140,100 square kilometers. The RCT will strictly comply with the CONSORT guidelines.

A total of 30 hospitals will be recruited into the RCT. The sampling proceeds as the following: (1) list all the existing hospitals in Anhui Province that perform joint replacement surgery; (2) randomly select 30 non-adjacent hospitals (hospitals not in the same city) from the hospitals listed; (3) randomly allocate the selected 30 hospitals into "intervention group" and "control group"(in a 1:1 ratio using a computer-generated random number sequence by third-party statistician); (4) the departments of orthopedics in all hospitals of intervention and control groups are regarded as participating departments, and all doctors in these participating departments are regarded as participating doctors. The reason for selecting hospitals not located in the same city is to prevent cross-contamination between hospitals in intervention and control groups.

### Eligibility criteria of participants

The study recruits both orthopedist and their patients. All orthopedists from the selected hospitals are encouraged to participate in this study. The inclusion criteria of patients include: (1) inpatient patients awaiting hip or knee joint replacement surgery; (2) has the ability to communicate and make independent decisions; (3) not less than 18 years old.

### Sample size

The primary outcome variable was the cost of MMs, and the anticipated MMs cost reduction rate was 20% with an alpha level of 0.05 and 90% power. Considering the cluster sampling efficiency loss (about 30%), design effect (about 2.45) and attrition of participants (about 20%), we estimated a total sample size of 1100 patients, 550 in each group.

### Intervention

#### Guiding framework

Development of the research protocol is based on a problem or deficiency list derived on a trans-theoretical framework which incorporates including mainly soft systems-thinking, information asymmetry, crisis-coping, dual delegation and planned behavior (Fig. 1). Soft systems-thinking guides systematically unwinding the complex MMs decision system into relatively manageable critical processes starting from symptoms to admission, diagnosis, treatment and then follow up after hospitalization; while the other theories inform identification of potential problems for each of the processes derived above. For example, we performed process-by-process scrutiny of potential moral risks caused by information discrepancies between doctors, patients and third payers according to information asymmetry.

**Fig. 1 Fig1:**
[figure not shown]
Framework of the study protocol. The research protocol framework includes two aspects including defects and problems identification (PP_1_–PP_4_ represent patient side problems, DP_1_–DP_4_ represent doctor side problems) and counter-measures development (PI_1_–PI_4_ represent patient intervention contents, DI_1_–DI_4_ represent doctor intervention contents)

#### Problems list

Based on the abovementioned framework, we worked out a list of most important problems/deficiencies with existing MMs via qualitative interviews and consensus group activities involving relevant doctors, patients and third payer staff (Table 1). The list comprises problems/deficiencies from both doctor and patient sides. The doctor side problems (DPs) fall into four categories, i.e., problems regarding evidence and guidelines (DP_1_), demand and preference analysis (DP_2_), procedures and items selection (DP_3_) and quality and effect evaluation (DP_4_). Similarly, patient side problems (PPs) concern analysis and judgment (PP_1_), symptom and history providing (PP_2_), communication and decision-making participation (PP_3_) and follow-up management (PP_4_).

**Table 1 Tab1:** Deficiencies with existing medical materials use

Code and title	Short description of deficiencies
DP_1_: Ignorance of evidence/guidelines	Doctors do not understand the latest research evidence and regulations regarding medical implants using (DP1a)
	Doctors do not have enough time in studying the latest professional development and progress owing to the heavy clinical works (DP1b)
	Doctor face difficulties to identify and abstract the latest useful evidence from numerous and rapidly growing literatures (DP1c)
	Doctors lack adequate foreign language proficiency contrasted by that the majority of medical research are published in English (DP1d)
DP_2_: Incomplete need/preference assessment	Doctors tend to conduct systematic and sophisticated auxiliary examinations for collecting evidence to protect doctors/hospitals from low probability "clinical accidents", rather than to improve the accuracy of diagnosis and treatment (DP2a)
	Doctors are keen at looking for physical determinants of diseases but pay less attention to psychological factors, family economic status and cost-effectiveness (DP2b)
	Doctors lack the ability of systematic analysis and multi-objective collaboration for patients’ needs and preferences (DP2c)
DP_3_: Inappropriate decision/selection	Doctors tend to order clinical diagnosis and treatment procedures (especially the MMs using) without clear indications (DP3a)
	Doctors often order a same and complete set of laboratory and imaging examinations to all their patients rather than selecting specific items according to the needs of specific patients (DP3b)
	Doctors tend to overuse specific MMs to cater to perceived demands of patients or sales agents (DP3c)
	Doctors tend to prescribe more or less certain MMs for demonstrating application of new technologies or to compliance to policy/management system requirements (DP3d)
	Doctors are often biased in selecting and recording patient symptoms and medical history, so as to justify application of specific diagnostic and therapeutic pathway and procedures (DP3e)
DP_4_: Difficult quality/effect monitoring	Lack of effective follow-up mechanism (DP4a)
	Lack of operable follow-up indicators and procedures (DP4b)
	Lack of adequate follow-up resources and technologies (DP4c)
PP_1_: Problematic cost-effect assessing	Patients can hardly obtain complete, objective and understandable information regarding treatment procedures and MMs use (PP1a)
	Patients do not have enough knowledge of relevant physiological/pathological mechanisms of disease development and thus lack the ability of independently comparing alternative procedures and making optimal decisions (PP1b)
	Patients and relatives have many irrational thinking patterns, such as "do everything one for health at any cost" (PP1c)
	Patients are often given misleading information about prognosis and diagnosis and treatment alternatives due to various reasons (PP1d)
PP_2_: Incomplete history provision	Patients often fail to fully recognize the importance of telling their doctors accurate history and symptoms (PP2a)
	Patients tend to conceal certain symptoms/history because of the presence of specific relatives or friends (PP2b)
	Patients may intentionally over-report/exaggerate some symptoms/history in order to obtain specific priority (such as earlier surgery) or compensation (e.g., medical insurance compensation) (PP2c)
	Patients may give biased report about their conditions to meet perceived expectations of doctors, relatives and friends (PP2d)
	Patients often lack the opportunity to check, revise and supplement symptoms and medical history collected in medical records (PP2e)
PP_3_: Inadequate clinical involvement	Patients have various suspicions and misunderstandings towards doctors and hospitals due to inaccurate self-media reports about negative cases (PP3a)
	Patients tend to "say good words in front of doctors " due to the influence of traditional Chinese culture (PP3b)
	Patients often avoid raising objections to doctors’ recommendations for diagnosis and treatment in order for fearing of upsetting doctors (PP3c)
PP_4_: Lack of follow-up mechanisms	Patients often do not keep in contact with the responsible doctors after their hospitalization (PP4a)
	Patients often have insufficient understanding of family rehabilitation and self-management after hospitalization (PP4b)
	Patients often seek for health services from different hospitals rather than a same hospital, which decreased the consistency/continuity of diagnosis, treatment and evaluation (PP4c)

#### Intervention ingredients

The intervention consists of two main components targeting at patients and doctors respectively. For patients, the intervention promotes option assessment (PI_1_), facts review and confirmation (PI_2_), self-expression (PI_3_) and follow-up management (PI_4_). For doctors, the intervention facilitates evidence promotion (DI_1_), demand feedback (DI_2_), procedure audit (DI_3_) and performance comparison (DI_4_). Each of these intervention ingredients is designed to tackle the doctor and patient-side problems with existing MMs as derived above. Taking the example of option assessment (PI_1_), it is designed to empower patients and/or their relatives to assess the benefits, dis-benefits and preferences over alternatives of MMs use. This is reached by providing: (a) all treatment options (especially MMs options) and explaining the benefits, dis-benefits and application indicators of each options; (b) tailored questions and answers regarding their current diseases and treatment and MMs use options; (c) structured "cost-utility" evaluation scale to help patients systematically evaluate the effects of different joint replacement and MMs use options on their physiological, psychological and social functions; and (d) concise and easily understandable "cost-utility" evaluation summaries of optimum matching scheme suitable for their own and the corresponding reasons. The target problems and main contents and procedures of each of the intervention ingredients are summarized in Table 2.

**Table 2 Tab2:** Summary intervention ingredients

Code and title	Short description of interventions
PI_1_: Cost–benefit evaluation aid	
Objectives	Help patients make a relatively systematic evaluation on the alternative diagnosis and treatment procedures including MMs use
Interventions	Display, to patient, diagnosis/treatment alternatives (especially options of MMs use) and corresponding advantages, disadvantages and indications
	Provide problem-solving cases so as to eliminate the problems and doubts that patients may have regarding their current conditions and MMs use
	Provide structured "cost-utility" rating scale to help patients systematically evaluate different joint replacement procedures/MMs on their physiological, psychological and social functions
	Provide easy-to-understand "cost-utility" evaluation summaries to help comparison and selection of different treatment/MMs options
PI_2_: Facts review and confirmation	
Objectives	Enable patients to review, confirm and supplement disease symptoms and history recorded by the doctor so as to correct and prevent selection biases and mistakes
Interventions	Remind patient of the importance of reporting and recording accurate symptoms and medical history
	Provide relatively "private", "independent" and convenient environment for patients to check and supplement information of symptoms and medical history without being affected by relatives, friends, doctors, etc.
	Ask patients to perform at least two times of "facts review and confirmation", one before treatment and MMs use and the other 1 week after discharge from hospital
PI_3_: Participation empowerment	
Objectives	Provide patients (via mobile app/personalized web page) with precautions, tips and skills in communicating with doctors
Interventions	Tell patients common misunderstandings and misperceptions about clinical practices and doctors/hospitals
	Tell patients the importance of fully and accurately reporting to doctors their conditions, especially the experience that doctors can not feel
	Tell patients that they can ask doctors, if they want, to discussion their health conditions and treatment in a private space free from potential disturbances
	Tell patients that it is their own interest to correct mistakes and fill gaps in the symptoms and medical history as recorded in their clinical records; Tell patients that they need to straightforwardly speak out their preferences, expectations and difficulties in selecting diagnosis and treatment options
PI_4_: Follow-up promotion/aid	
Objectives	Encourage and help patients practice self-care management after discharge and cooperate in follow-up visits and evaluation feedbacks
Interventions	Tell and encourage patients, via a daily text message for 1 month after discharge, how to practice post operation rehabilitation and other self-care activities
	Ask patients questions about their satisfaction and effectiveness of the previous inpatient care and problems encountered after the discharge
	Give feedback, via the daily text message again, to patients on the follow-up query and in particular, on helping them solve problems encountered
DI_1_: Evidence/guideline reminding	
Objectives	Improve practice quality and compliance with relevant policies, professional guidelines and use of research evidences
Interventions	Post bulleted key requirements of relevant policy/guideline together with hyperlinks to detailed files of these policy/guidelines on the homepage of the clinical support system to be described later
	Display a pop-up window containing indications or view points for doctors to check and confirm their decisions on material use
	Maintain a bimonthly briefing of newly published evidences in relevant fields on the aforementioned homepage
DI_2_: Need/preference presentation	
Objectives	Help doctors better understand their patient’s needs, expectations and preferences
Interventions	Present doctors with a brief report summarizing the main points of medical record that have been confirmed, amended and complemented by the patients
	Present doctors with a list of the preference ratings of potential treatment options (including options of MMs use) given by a specific patient under concern
DI_3_: Diagnosis/treatment peer-audit	
Objectives	Introduce a pragmatic mechanism of learning from real cases and technical assistance between peer doctors
Interventions	Form a peer-review group consisting of mainly the participating doctors themselves and a few well-known local experts from outside the study participants
	Perform a monthly “cross-review”, in which two patients were randomly selected as the review cases for each participating doctor from all the patients he/she has served in the past month and then reviewed anonymously by one of the other peer group members
	Email the results of the above peer review (comments and suggestions regarding the two selected cases) to the corresponding doctor
DI_4_: Performance feedback	
Objectives	Give doctors a bimonthly feedback and encourage good performance and inform identification and overcome of potential problems/shortcomings
Interventions	Form a set of agreed performance indicators by involving all the participating doctors in the intervention group
	Post top 10 performance stars on the homepage of APP for patients and on the homepage of the support system for doctors, and update it every 2 months
	Send a doctor-specific feedback email, again bimonthly, to each participating doctors in the intervention group

#### Electronic support

Implementation of the intervention is supported by an online platform established and maintained by the Quality Assurance Center for Medical Care in Anhui Province, a smartphone-based application program (APP) and a web-based clinical support system (CSS). The CSS is designed for use by doctors; while the APP, for patients.

### Control

The participants in the control group receive the existing medical services without any additional consultation and feedback services adopted in the intervention group.

### Study and data integrity

For the integrity of study and data, the study design follows the CONSORT (Consolidated Standards of Reporting Trials) statement.

### Measures

As shown in Table 3, the primary outcome measures for evaluating the intervention include: (1) Cost of medical materials assessed using questionnaire custom-designed for this study at 6 months and 12 months after discharge, these data will be used to calculated cost-effectiveness; (2) Quality-of-life assessed using the EQ-5D-5L scale at discharge, and 6 months, 12 months and 18 months after discharge. The secondary outcome measures include: (1) Peer expert audit score assessed using a custom-designed questionnaire at 6 months after discharge; (2) Quality control inspection score assessed using a custom-designed questionnaire at 6 months after discharge; (3) Patient awareness rate (treatment schedule, surgical risk, material selection, etc.) assessed using a custom-designed questionnaire at discharge, and 6 months, 12 months and 18 months after discharge; (4) Patient satisfaction assessed using a custom-designed questionnaire at discharge, and 6 months, 18 months after discharge; (5) Total medical expense assessed using a custom-designed questionnaire at 6 months and 18 months after discharge.

**Table 3 Tab3:** Variables and time points for outcome measures

Measure	Time point (month after discharge)			
	Discharge day	6 months	12 months	18 months
Cost of medical materials		√		√
Quality-of-life	√	√	√	√
Peer expert audit score		√		
Quality control inspection score		√		
Patient awareness rate	√	√	√	√
Patient satisfaction	√	√		√
Total medical expense		√		√

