### Data collection and analysis

The data for intervention evaluation will be collected from two sources: patients' medical records retained by the participating hospitals (e.g., electronic medical records, paper treatment records and MMs charge records) and patients' baseline and follow-up health related information via multi-stage surveys. For medical records, we first periodically centralized copy electronic documents and borrow paper documents from hospital, and then we arrange two uniformly trained graduate students (each hospital) independently extract data according to the pre-designed structured "data table". When inconsistencies arise, they negotiate to reach a consensus. The baseline and follow-up surveys will be conducted by uniformly trained graduate students in the form of telephone interviews with structured questionnaires. The follow-up strives to reach less than 20% attrition of participants by means of at least 3 times of reminding messages and 5 times of telephone calls at different time and days. The researchers are trained to record reasons of attrition for each of the patients they have lost. Characteristics of patients lost to follow-up will be analyzed and compared to those who finish the interventions to assess potential attrition biases. Data analysis will focus mainly on comparing the differences in overall and specific indicators of appropriateness of joint replacement surgery and MMs used between the intervention and control arms.

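### The outcome schedule shows no EQ-5D-5L before surgery and first ICFS contact and is not reconciled with the planned baseline survey; no pre-randomisation hospital MMs cost is planned either

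*Protocol article*

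**What the plan says.** The Measures section names two primary outcomes. Quality of life is given as "Quality-of-life assessed using the EQ-5D-5L scale at discharge, and 6 months, 12 months and 18 months after discharge". Material cost is given as "Cost of medical materials assessed using questionnaire custom-designed for this study at 6 months and 12 months after discharge". Table 3 repeats the quality-of-life times, and its first column is the discharge day. (For the second cost assessment Table 3 has 18 months where the text has 12. That is a separate discrepancy; neither time precedes surgery.)

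The eligibility criteria admit "inpatient patients awaiting hip or knee joint replacement surgery". In Table 2, the facts review (PI2) is done at least twice, "one before treatment and MMs use and the other 1 week after discharge from hospital". Option assessment (PI1) helps patients weigh the MMs alternatives, and DI2 shows doctors the patient's preference ratings.

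The data collection section lists as a source "patients' baseline and follow-up health related information via multi-stage surveys", and adds: "The baseline and follow-up surveys will be conducted by uniformly trained graduate students in the form of telephone interviews with structured questionnaires". It does not say when the baseline survey takes place or whether it contains EQ-5D-5L. It also lists MMs charge records as a source.

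Thirty hospitals are allocated "in a 1:1 ratio using a computer-generated random number sequence by third-party statistician". The article mentions no stratification or matching and no hospital cost data from before randomisation.

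**The concern.** A patient awaiting joint replacement who is next measured at discharge has had the operation in between and, in the intervention arm, has met part of the ICFS. The discharge EQ-5D-5L is therefore an early outcome. The article promises a baseline survey, yet its only measurement schedule has no place for one. One reader could take discharge as the baseline; another could assume a pre-operative EQ-5D-5L that is not listed.

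The choice has consequences. A change from discharge, or adjustment for the discharge value, would subtract whatever effect is already present at discharge. A pre-operative value would instead sharpen the comparison and let the arms be checked for case mix. That check has some weight here: hospitals are randomised, and the article does not say that patients are identified before their hospital's allocation is known. A pre-operative value that is not collected cannot be recovered later, so this cannot be left to the analysis stage.

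For cost the question is different. A patient has no MMs cost for the index operation before that operation. Each hospital does have a usual level of MMs spending, and with 15 hospitals per arm chance differences in that level can be noticeable.

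**Working it through.** **1. Order of events for a patient in the intervention arm**

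| Step | Source | EQ-5D-5L scheduled? |
|---|---|---|
| Enters while awaiting surgery | Eligibility criteria | No |
| First facts review, before treatment | Table 2, PI2 | No |
| Surgery and MMs use | Follows from the two rows above | No |
| Discharge | Measures, Table 3 | Yes, first value |
| Second facts review, 1 week later | Table 2, PI2 | No |
| 6, 12 and 18 months | Measures, Table 3 | Yes |
| Baseline survey | Data collection section, undated | Not stated |

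The first scheduled value follows surgery and some, but not all, of the patient-side intervention.

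**2. What would be lost if discharge served as baseline**

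Let s be the effect at discharge as a share of the later effect, and b the slope of the later value on the discharge value. A change score keeps 1 − s of the later effect; adjustment keeps 1 − b·s. Assumed values: s from 0.25 to 1, b = 0.5.

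- Change score: 1 − 0.25 = 75%, down to 1 − 1 = 0%.
- Adjustment: 1 − 0.5 × 0.25 = 87.5%, down to 1 − 0.5 × 1 = 50%.
- If s = 0, nothing is lost.

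**3. What a pre-operative EQ-5D-5L would gain**

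Patient-level residual variance is multiplied by 1 − r². With r assumed at 0.3 to 0.5, the factor is 0.91 to 0.75, a cut of 9% to 25%.

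**4. The ICC implied by the plan's design effect**

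The sample size section gives 1100 patients, a design effect of about 2.45 and attrition of about 20%; there are 30 hospitals. Patients per hospital: 1100/30 = 36.7, or 36.7 × 0.8 = 29.3 after attrition. From design effect = 1 + (m − 1) × ICC:

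- m = 29.3: 1.45/28.3 = 0.051.
- m = 36.7: 1.45/35.7 = 0.041.

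The article states no ICC; 0.05 is used below as an assumption that agrees with the stated design effect. The total of 1100 cannot be reproduced, because no SD or coefficient of variation is given, but nothing here depends on it.

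**5. What a prior hospital mean cost would gain**

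Variance of a hospital mean, in patient-level units: 0.05 + 0.95/29.3 = 0.0824. A hospital-level covariate with correlation r reduces only the first term, to 0.05 × (1 − r²).

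| r (assumed) | Variance | Ratio to 0.0824 | Reduction |
|---|---|---|---|
| 0.5 | 0.0375 + 0.0324 = 0.0699 | 0.85 | 15% |
| 0.7 | 0.0255 + 0.0324 = 0.0579 | 0.70 | 30% |
| 0.8 | 0.0180 + 0.0324 = 0.0504 | 0.61 | 39% |

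The same precision without the covariate would need 0.0824/0.0699 = 1.18 to 0.0824/0.0504 = 1.63 times as many hospitals.

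**6. Chance imbalance with 15 hospitals per arm**

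Under simple 1:1 allocation, the arm difference in a hospital-level factor has SD √(2/15) = 0.365 hospital-level SDs. The probability that it exceeds 0.5 in either direction is P(|Z| > 0.5/0.365 = 1.37) = 0.17. If the factor is hospital mean cost at an ICC of 0.05, 0.5 hospital-level SD equals 0.5 × √0.05 = 0.11 patient-level SD.

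**The case against.** A reader might infer that neither primary outcome has any pre-intervention measurement and that the planned analysis is therefore biased. The article does not support that, for these reasons:

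- The baseline survey collects health-related information and may well include EQ-5D-5L. A journal article commonly leaves questionnaire content to the full protocol, and Table 3 is headed in months after discharge, so it need not list baseline items.
- A missing patient-level baseline for MMs cost is no defect, because that cost does not exist before the operation.
- The article plans no change score, no adjustment for the discharge value and no QALY analysis. It says only that the cost data will be used to calculate cost-effectiveness. Discharge is already listed as an outcome time.
- Randomised arms can be compared validly at each follow-up time without a baseline. Between-hospital variation is already allowed for through the design effect of 2.45, so the 17% in step 6 describes ordinary sampling variation and not bias.
- Covariates, and any restriction on the allocation, may be set out in documents not shown.

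All of this stands, and it limits the point to precision and control of imbalance. It does not remove the mismatch: the schedule is set out for all seven measures, a baseline survey is named beside it, and nothing connects the two. A later analysis plan can choose covariates, but it cannot supply a pre-operative value that was never collected.

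**Conclusion.** The point holds as an unreconciled schedule with an inexpensive improvement attached; it is not an error that invalidates the trial. The schedule shows no EQ-5D-5L before surgery and first ICFS contact, and the discharge value would be unsuitable as a baseline because it could absorb part of the effect. Whether the baseline survey already covers EQ-5D-5L cannot be told from the article.

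The sizes rest on assumptions. The 9% to 25% cut in EQ-5D-5L residual variance assumes a correlation of 0.3 to 0.5. The 15% to 39% cut in the variance of the cost contrast assumes an ICC of about 0.05 and a cluster-level correlation of 0.5 to 0.8. The possible dilution in step 2 arises only if discharge is used as baseline and an effect is already present then. The hospital cost covariate is an optional gain in precision.

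**What to change.** State when the baseline survey takes place and what it contains. Collect EQ-5D-5L in it at admission, before the patient's first ICFS contact; show it as a baseline column in Table 3; name it as a covariate for the quality-of-life comparison; and keep discharge as a follow-up time point.

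Optionally, extract each hospital's mean MMs cost per hip or knee case for a fixed period before randomisation from the charge records, and adjust the cost comparison for it.

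The cost is one short questionnaire added to a survey already planned and a modest look-back extraction from records already being accessed.
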